### Assessment of postoperative infection

2.5

Postoperative infections will be evaluated by an independent, professionally trained review panel, including attending or higher–level cardiac surgeons, ICU physicians, and infectious disease specialists. All adjudicators will remain blinded to patients' lactate exposure group assignment and TWA lactate values. Postoperative infections to be recorded include sepsis, pulmonary infection, surgical site infection, mediastinitis, and endocarditis. The frequency of postoperative infection assessment is shown in Table 1.

**Table 1 T1:** Schedule of data collection and measurement time points.

Outcome measure Time		Visit 1	Visit 2	Visit 3	Visit 4	Visit 5	Visit 6	Visit 7	Visit 8
		Presurgery	During operation	Postoperative day 1	Postoperative day 2	Postoperative day 3	Postoperative day 7	Postoperative day 14	Postoperative day 30
Enrollment	Eligibility screening	×							
	Informed consent	×							
	Demographic characteristics	×							
	Baseline measures	×							
	Preoperative comorbidities	×							
Intraoperative	Surgery-related variables		×						
	physiological and anesthesia-related		×						
Postoperative	laboratory indices			×					
	SIRS score			×					
	GCS score			×	×	×	×	×	×
	Sequential Organ Failure Assessment Score			×	×	×	×	×	×
	Postoperative infection			×	×	×	×	×	×
	Acute kidney injury				×		×		
	Liver injury					×			
	ICU length of stay			×	×	×	×	×	×
	Mechanical ventilation duration			×	×	×	×	×	×
	Postoperative Adverse Events	Safety outcomes will be assessed from admission through 30 days post-surgery							

SIRS score, systemic inflammatory response syndrome score; GCS score, glasgow coma scale score.

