Serum lactate is a complex biomarker. Lactate levels during CPB surgery typically serve as an indicator of overall physiological stress, surgical complexity, and perfusion adequacy (6, 7). The nonpulsatile perfusion pattern during CPB can lead to organ hypoperfusion, ischemia–reperfusion injury, and systemic inflammatory responses, all of which may enhance lactate metabolism and cause peripheral lactate accumulation (8, 9). In this study, we hypothesize that lactate serves as both a marker of underlying pathophysiological processes and a potential mediator of immunosuppression. At high concentrations (e.g., 12.5 mM), it enhances hypoxia-inducible factor 1-alpha (HIF-1*α*) expression, while mitigating acute inflammatory injury, which also suppresses mast cell activation via monocarboxylate transporter 1 (MCT-1) and pH-dependent pathways, thereby increasing the risk of infection (10). Furthermore, lactate impairs T-cell function by inhibiting migration, reducing the cytotoxic activity of neutrophil, cluster of differentiation 4-positive T cells (CD4^+^) and cluster of differentiation 8-positive T cells (CD8^+^) T cells, promoting CD4^+^ T cell differentiation toward the T helper 17 cells (Th17) subset, and inducing interleukin-17 (IL-17) accumulation, collectively leading to the occurrence of surgical site infections and other infections (11, 12). In sepsis, lactate is closely associated with diagnosis, progression, and treatment, and it further reduces immune cell activity by inducing mitochondrial dysfunction and impaired oxygen consumption, contributing to multiple organ dysfunction (13). Lactate can also suppress nuclear factor *κ*B (NF-*κ*B) transcriptional activity and cytokine production in mast cells, whereas enhancing glycolysis and adenosine triphosphate (ATP) generation can restore immune function (14). Previous studies have also indicated that acidification is an independent virulence mechanism for pneumonia barrier disruption and inflammatory dysregulation, which may directly contribute to the development and progression of bacterial pneumonia, whereas maintaining normal pH represents an effective therapeutic strategy for preserving barrier integrity and immune response (15). Based on the above evidence, a mechanistic diagram (Figure 1) was constructed to integrate these proposed mechanisms and illustrate how cardiopulmonary bypass-related lactate elevation may promote postoperative infection through lactate-mediated immune dysregulation. Because lactate measurement is inexpensive, reproducible, and routinely monitored during the perioperative period, it has inherent advantages as a potential biomarker for postoperative infection risk.

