### Exposure

2.4

Trained research personnel will measure patients' blood lactate levels during cardiopulmonary bypass using Radiometer ABL90 FLEX blood gas analyzer. The procedures are as follows:
During cardiopulmonary bypass, arterial blood samples will be collected from the radial or femoral artery at the following time points: T_1_, after the initiation of cardiopulmonary bypass, when coronary perfusion with cardioplegic solution induces cardiac arrest; T_2_, T_3_, …, Tn, every 1 h after the start of bypass; T_n_ _+_ _1_, 10–20 min before the end of bypass; and T_n_ _+_ _2_, within 5 min after the end of bypass. Here, T_n_ represents the last full-hour sampling point during bypass. Additionally, extra samples will be collected whenever there is a sudden increase in lactate during CPB (e.g., following hypotension or hypoperfusion events). At least four lactate measurements during cardiopulmonary bypass are required for TWA lactate calculation.Within 1 min of blood collection, lactate levels will be measured using the blood gas analyzer and recorded in mmol/L to one decimal place. If duplicate measurements are performed at the same time point, the mean value will be used as the final lactate measurement.The time-weighted average lactate (TWA) will be calculated from the lactate values obtained at different time points. TWA is defined as the area under the curve of lactate levels over time divided by the total observation interval, using the formula:$$TWA=\frac{1}{T}\overset{n=1}{\underset{i=1}{\sum }}\;\left(\frac{v_{i}+v_{i+1}}{2}\right)\Delta t_{i}$$Evidence from previous cardiac surgery cohort studies has reported that lactate concentration of >2.0 mmol/L during surgery or in the early postoperative period are already associated with increased postoperative morbidity and mortality. Accordingly, based on the available evidence, recommendations from international sepsis guidelines, TWA lactate of 2.0 mmol/L is selected as the prespecified cutoff for exposure classification. TWA lactate ≥2.0 mmol/L during CPB will be categorized into the exposure group, with the TWA lactate <2.0 mmol/L classified into the non-exposure group (24–27). Lactate will also be analyzed as a continuous variable in the subsequent analyses.We will also calculate the following lactate indices to comprehensively characterize lactate exposure:

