#### Sepsis (Sepsis-3)

2.5.2

It is defined as an acute change of ≥2 points in the Sequential Organ Failure Assessment (SOFA) score caused by infection within 30 days postoperatively. The SOFA score is a scoring system used to evaluate the severity of organ dysfunction in critically ill patients. It covers six major organ systems: respiratory, cardiovascular, hepatic, renal, neurological, and coagulation. Each organ system is scored from 0 to 4, with higher scores indicating more severe organ dysfunction (29–31).

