Postoperative data: Postoperative 24 h: arterial blood gas analysis, hemoglobin (g/L), platelet count (10⁹/L), lymphocyte count (10⁹/L), neutrophil count (10⁹/L), 24-hour lactate clearance (%), 24-hour SIRS score, postoperative complications, PCT (ng/mL), CRP (mg/L). Duration of mechanical ventilation (hours), ICU length of stay (hours). Creatinine (μmol/L) within 7 days postoperatively, and alanine aminotransferase (ALT, U/L) and aspartate aminotransferase (AST, U/L) levels within 3 days postoperatively.

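### The infection panel's stated blinding names only exposure group and TWA lactate, so the plan does not ensure that judgement-based infection decisions are made without other lactate results

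*Protocol article*

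**What the plan says.** Section 2.5 assigns infection assessment to an "independent, professionally trained review panel, including attending or higher–level cardiac surgeons, ICU physicians, and infectious disease specialists". Its blinding rule keeps every adjudicator unaware of each patient's "lactate exposure group assignment and TWA lactate values". Both masked items are derived quantities. Under section 2.4, TWA "will be calculated from the lactate values obtained at different time points", and peak lactate, lactate load and 24-hour clearance are derived as well. Section 2.9 uses lactate load and peak lactate as alternative exposures in the sensitivity analyses.

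Lactate sits among the blood gas data. For the bypass samples, "lactate levels will be measured using the blood gas analyzer" (section 2.4), and section 2.11.1 records lactate together with pH, hematocrit and glucose. The postoperative data block begins "Postoperative 24 h: arterial blood gas analysis" and also contains 24-hour lactate clearance, PCT and CRP.

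Sepsis (section 2.5.2) requires a SOFA change of at least 2 points "caused by infection within 30 days postoperatively". Pulmonary infection (section 2.5.1) includes a fever item that counts only if nothing else explains the fever. None of the five definitions lists lactate, and the six SOFA organ systems named in section 2.5.2 do not include it.

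**The concern.** The rule masks two summaries of lactate and is silent on the rest. That matters because the exposure is lactate and part of the outcome rests on clinical judgement. The Introduction itself says: "In sepsis, lactate is closely associated with diagnosis, progression, and treatment". It also describes lactate as routinely monitored around surgery, so the results are likely to be in the hospital record. A panel of intensivists and infection specialists weighing a borderline case could take a high value as support for infection.

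If that happened, the error in the primary outcome would depend on exposure. False infections would collect among patients with high lactate, and the odds ratio would most plausibly move upward. Covariate adjustment could not remove the error, because it lies in how the outcome is labelled and not in confounding.

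**Working it through.** **1. What the rule covers.**

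| Lactate item | Where defined or collected | Named in the blinding rule? |
|---|---|---|
| Exposure group, TWA | 2.4 | Yes |
| Timed bypass values | 2.4, 2.11.1 | No, but TWA is computed from them |
| Peak lactate, lactate load | 2.4, 2.9 | No, but they come from the same values |
| End-of-surgery and 24-hour lactate, clearance | 2.4, 2.8.2, 2.11.1 | No |

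Faithful masking of TWA implies withholding the timed bypass values, since they nearly determine it. The end-of-surgery and 24-hour results are not implied in this way, so they are the clearest gap.

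**2. Whether other text closes it.** No section masks further lactate results, and none describes the adjudication file. Section 2.11.4 puts lactate levels and infection diagnoses under one double-check without saying that they are kept apart. The Discussion describes verification by study personnel and attending physicians with no mention of blinding.

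**3. The plan's own numbers.** Section 2.3 gives a baseline risk p1 = 0.104, OR 2.75, two-sided alpha 0.05 and power 0.90.

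- p2 = 2.75 × 0.104 / (1 − 0.104 + 2.75 × 0.104) = 0.286 / 1.182 = 0.242.
- The pooled two-proportion formula without continuity correction gives 156 per group, matching the plan, with power 0.900.

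**4. Illustration of size.** The upgrade rates u are assumptions; the article gives none. Suppose there is no true effect, the true risk is p in both groups, there are 156 patients per group, and a fraction u of non-infected exposed patients is upgraded to infected.

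- Observed exposed risk: q = p + u(1 − p).
- Observed OR: [q / (1 − q)] / [p / (1 − p)].
- Example: p = 0.104 and u = 0.02 give q = 0.104 + 0.02 × 0.896 = 0.1219, so OR = 0.1388 / 0.1161 = 1.20.
- Patients upgraded: 156 × 0.896 × u.

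| u | Patients upgraded (p = 0.104) | OR, p = 0.104 | Chance of P<0.05, harmful direction | OR, p = 0.155 | Chance of P<0.05, harmful direction |
|---|---|---|---|---|---|
| 1% | 1.4 | 1.10 | 4% | 1.07 | 4% |
| 2% | 2.8 | 1.20 | 7% | 1.13 | 6% |
| 3% | 4.2 | 1.30 | 11% | 1.20 | 9% |
| 5% | 7.0 | 1.51 | 22% | 1.34 | 16% |

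The nominal chance in that direction is 2.5%. The second baseline, 15.5%, is the upper end of the incidence range in section 2.3. If the panel also detected true infections unequally (assumed sensitivity 0.95 in exposed, 0.85 in unexposed), the OR at p = 0.104 would be 1.36 at u = 2% and 1.73 at u = 5%.

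**The case against.** The strongest reply is that the article never says adjudicators see lactate. It states the principle, an independent, trained and blinded panel, and the make-up of adjudication packets commonly belongs in a charter or full protocol. Honest blinding to TWA already requires withholding the bypass values. What remains is postoperative lactate, which is not the exposure: a 24-hour value does not reveal a bypass average. The planned data list no lactate item after 24 hours.

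The definitions also narrow the route. Pneumonia needs an infiltrate, which lactate cannot supply, and endocarditis needs positive cultures plus echocardiographic evidence. Adding sepsis in a patient who already has another component does not change the composite.

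Most of this stands. A reader might infer that the panel works from records showing lactate, so that the exposure is built into the primary outcome. The article does not support that: access would have to be read out of silence. It also does not say that postoperative gases are run on the analyzer used for bypass samples, or that the panel scores SOFA from full blood gas reports.

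What the reply does not remove is that section 2.5 goes beyond the general principle. It lists what is masked, and the list is narrower than the lactate data the study collects. Using 24-hour lactate could still carry exposure into the outcome through its correlation with bypass lactate; section 2.6 treats lactate clearance as a mediator of the exposure.

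**Conclusion.** The point holds as a gap in the stated safeguard, not as a demonstrated bias. The blinding rule does not expressly extend beyond group and TWA, so the plan does not ensure that the judgement-based parts of the infection definitions are decided without lactate. The gap is clearest for end-of-surgery and 24-hour lactate and clearance.

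Any effect depends on two things the article does not state: that adjudicators see these values, and that the values sway borderline decisions. If both held, the odds ratio would most plausibly be too high. Under the assumed upgrades of 2% to 5% with no true effect, it would be 1.20 to 1.51 at 10.4% baseline risk and 1.13 to 1.34 at 15.5%. These figures come from an unadjusted comparison of two equal groups and only show scale: about 3 to 7 upgraded patients at the lower baseline are enough. They do not estimate what will happen in this study.

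**What to change.** Amend the blinding sentence in section 2.5 so that adjudicators are blinded to exposure group, TWA lactate, and all intraoperative and postoperative lactate results and indices derived from them (peak, load, clearance). State that these fields are masked in the adjudication file and that the oxygenation and other SOFA items are supplied without them. Removing pH or base excess is not needed.

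The cost is one sentence in the plan and some extra work by data staff in preparing files for 346 patients, including checking blood gas printouts and notes. No stated infection definition uses lactate, so the panel loses nothing it needs.

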#### Postoperative pulmonary infection

2.5.1

It is defined as the presence of new or progressive infiltrates on chest radiography or CT within 30 days postoperatively, along with at least two of the following three criteria: (1) fever >38 °C without other causes; (2) white blood cell count >12  ×  10⁹/L or <4  ×  10⁹/L; (3) purulent secretions or positive sputum culture results (28).

#### Sepsis (Sepsis-3)

2.5.2

It is defined as an acute change of ≥2 points in the Sequential Organ Failure Assessment (SOFA) score caused by infection within 30 days postoperatively. The SOFA score is a scoring system used to evaluate the severity of organ dysfunction in critically ill patients. It covers six major organ systems: respiratory, cardiovascular, hepatic, renal, neurological, and coagulation. Each organ system is scored from 0 to 4, with higher scores indicating more severe organ dysfunction (29–31).

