Currently, studies on the association between lactate levels and the risk of postoperative infection in cardiac surgery are limited and the evidence is insufficient. Studies on lactate and cardiac surgical outcomes have primarily focused on organ dysfunction, mortality, intensive care unit (ICU) length of stay, and postoperative mechanical ventilation time (16, 17). In the field of infection research, investigations of lactate have mainly centered on its role in assessing sepsis severity and prognosis (18). Moreover, a retrospective study of adult cardiac surgery found that there was no significant difference in the incidence of postoperative infection between the high lactate group and the low lactate group (19). However, another more recent retrospective study found that patients with postoperative pneumonia had significantly higher perioperative lactate levels than those without pneumonia (20). Therefore, in this particular population of cardiovascular surgery patients, the lactate levels during surgery and the incidence of various types of postoperative infections, such as pulmonary infection, surgical site or mediastinal infection, and infective endocarditis, still lack large-scale prospective cohort studies.

In patients undergoing cardiac surgery with CPB, evaluating the predictive value of lactate exposure during CPB as an early warning indicator for postoperative infection may help address current evidence gaps. It can provide a scientific basis for perioperative management, early infection identification, and individualized prevention strategies, thereby reducing complication rates and healthcare burdens. Therefore, the relationship and predictive value between lactate and postoperative infection warrant validation through larger, prospective cohort studies, underscoring the clear clinical and scientific significance of the present research.

This study is a single-center, prospective cohort study designed to investigate the association between time-weighted average (TWA) lactate levels during CPB and postoperative infection in patients undergoing cardiac surgery. The null hypothesis of this study is that the time-weighted average lactate level during CPB is not associated with postoperative infection in patients undergoing cardiac surgery with CPB.

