#### Surgical site infection

2.5.3

It is defined as the occurrence of at least one of the following in the surgical incision within 30 days postoperatively: (1) purulent drainage from the deep incision, not originating from the organ/space of the surgical site; (2) spontaneous dehiscence of the deep incision or surgical opening by a surgeon due to infection, accompanied by at least one of the following: fever (>38 °C), localized pain, or tenderness; (3) evidence of abscess or other deep incision infection detected by direct examination, reoperation, histopathology, or imaging; (4) diagnosis of deep incision infection by the surgeon or attending physician (32).

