#### Primary outcome

2.8.1

The 30-day follow-up window was selected to encompass the main perioperative recovery period, during which most clinically apparent infections related to the index surgery are expected to be identified, while preserving temporal proximity to the transient intraoperative lactate exposure. With longer follow-up, infections may be increasingly influenced by post-discharge exposures, rehospitalization, subsequent invasive procedures, and additional treatments, thereby weakening their relationship with TWA lactate exposure. Although the specific mechanisms differ, all these infections share common pathways of immunosuppression and impaired host defense. The types of postoperative infections include sepsis, pulmonary infection, surgical site infection, mediastinitis, and infective endocarditis. The postoperative follow-up time is shown in Table 1.

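### Infections outside the four site definitions enter the primary composite only through sepsis, and so only with organ dysfunction; record the source of each sepsis event and test its influence

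*Protocol article*

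**What the plan says.** Section 2.5 of the protocol article lists what is counted: "Postoperative infections to be recorded include sepsis, pulmonary infection, surgical site infection, mediastinitis, and endocarditis". Section 2.8.1 gives the same five types under the primary outcome ("The types of postoperative infections include sepsis, pulmonary infection, surgical site infection, mediastinitis, and infective endocarditis"), and 2.8.2 names them again as separately analysed components. The verb used in these lists could be read as open-ended, but the same five appear each time and only these five are defined, so the list reads as closed.

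Four components are tied to a site:

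- Pulmonary infection (2.5.1) needs new or progressive infiltrates plus two of three further criteria.
- Surgical site infection (2.5.3) has four criteria, all concerning the deep incision. The first is "purulent drainage from the deep incision, not originating from the organ/space of the surgical site" and the last is "diagnosis of deep incision infection by the surgeon or attending physician".
- Mediastinitis (2.5.4) needs involvement of the sternal bone.
- Infective endocarditis (2.5.5) needs both a positive blood culture and echocardiographic evidence.

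The fifth, sepsis (2.5.2), has no site restriction. It is an "acute change of ≥2 points in the Sequential Organ Failure Assessment (SOFA) score caused by infection within 30 days postoperatively". On the SOFA score the section says: "It covers six major organ systems: respiratory, cardiovascular, hepatic, renal, neurological, and coagulation".

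**The concern.** An infection that meets none of the four site definitions has one way into the primary outcome: it must come with a SOFA change of at least 2 points. Superficial sternal or harvest-site wound infection, urinary infection and bloodstream infection without echocardiographic endocarditis all fall here. Whether such an infection is an event depends on organ function.

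The protocol does not treat organ function as unrelated to the exposure. The Introduction says of earlier work: "Studies on lactate and cardiac surgical outcomes have primarily focused on organ dysfunction, mortality". Section 2.6 places hepatic and renal dysfunction among the mediators, downstream of TWA lactate. If an exposed patient with, say, a urinary infection is more likely to gain 2 SOFA points from it than an unexposed patient with the same infection, the first is counted and the second is not. Part of any observed association would then reflect how severe infections were rather than how many occurred. The covariate adjustment does not address this, because mediators are deliberately left out of the model.

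There is also a labelling issue. A reader who sees *surgical site infection* and *postoperative infection* in the results will assume a broader outcome than the one counted.

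**Working it through.** **Which infections count, by definition**

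| Infection | Counts without a SOFA change? | Route into the composite |
|---|---|---|
| Pulmonary, meeting 2.5.1 | yes | own component |
| Deep incisional | yes | 2.5.3 |
| Sternal bone involved | yes | 2.5.4 |
| Endocarditis, culture and echocardiography | yes | 2.5.5 |
| Superficial wound | no | 2.5.2 only |
| Bloodstream, no echocardiographic endocarditis | no | 2.5.2 only |
| Urinary | no | 2.5.2 only |

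**The plan's own figures, for scale (2.3)**

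Baseline risk p1 = 0.104 and odds ratio 2.75 give

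p2 = 2.75 × 0.104 / (1 − 0.104 + 2.75 × 0.104) = 0.286 / 1.182 = 0.242.

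The pooled two-proportion formula, two-sided α 0.05 and power 0.9, gives 156 per group, as stated. The planned difference is 156 × (0.242 − 0.104) = 21.5 events per 156 patients.

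**Illustration under no true effect**

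The document gives none of the following inputs except 10.4%; the rest are assumptions.

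- Listed-site infection: 10.4% in both groups. The protocol uses this figure as the overall baseline infection rate; it is borrowed here.
- Other-site infection among the remaining 89.6%: o = 3%, 5% or 8%, the same in both groups.
- Probability that an other-site infection brings a qualifying SOFA change: q0 (unexposed) and q1 (exposed).

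Risk in each group: p = 0.104 + 0.896 × o × q. The spurious odds ratio is the ratio of the two odds.

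Example, o = 8%, q0 = 0.2, q1 = 0.5:

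- unexposed: 0.104 + 0.896 × 0.08 × 0.2 = 0.1183
- exposed: 0.104 + 0.896 × 0.08 × 0.5 = 0.1398
- odds ratio = (0.1398 / 0.8602) / (0.1183 / 0.8817) = 1.21

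| q0 vs q1 | o = 3% | o = 5% | o = 8% |
|---|---|---|---|
| 0.2 vs 0.2 | 1.00 | 1.00 | 1.00 |
| 0.2 vs 0.3 | 1.03 | 1.05 | 1.07 |
| 0.1 vs 0.3 | 1.06 | 1.09 | 1.15 |
| 0.2 vs 0.5 | 1.08 | 1.14 | 1.21 |

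The excess in the exposed group is 156 × 0.896 × o × (q1 − q0). That is 0.4 events per 156 patients at the smallest unequal setting (o = 3%, 0.2 vs 0.3) and 3.4 at the largest (o = 8%, 0.2 vs 0.5).

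**A second set of assumptions**

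Fix the unexposed composite at 10.4% overall and let other-site infections occur in 2% to 6% of each group. Then 25% vs 50% gives 1.05 to 1.16, and 20% vs 60% gives 1.09 to 1.27. A deliberately extreme 10% vs 70% gives 1.13 to 1.40.

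**The case against.** Four arguments carry weight.

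1. *Attribution.* Section 2.5.2 counts only a SOFA change that infection caused. Points arising from bypass hypoperfusion alone do not qualify, and the panel is blinded to lactate group and TWA values (2.5). A reader might infer that exposed patients become events simply because bypass raises their SOFA score; the wording does not support that. What remains is narrower: a real infection may be more likely to add 2 points in a patient with less organ reserve. Blinding cannot remove that, because it lies in the definition and not in the panel's judgement.
2. *Direction.* Organ dysfunction already present after bypass raises the level from which an acute change is measured, which could make a further 2-point rise harder to reach in exposed patients. The upward direction is plausible, not established.
3. *Pathway.* The protocol hypothesises that lactate impairs host defence, and the Introduction connects it with multiple organ dysfunction in sepsis. Faster progression from infection to sepsis is partly the effect under study. That makes this in part a question of interpretation, severity against incidence, rather than pure artefact.
4. *Scope.* A composite of serious infections that omits uncomplicated superficial or urinary infection is a coherent choice. Restricting sepsis to listed sites would make it nearly redundant and drop septic bloodstream infection without endocarditis; adding milder infections would change the endpoint. Either is a trade-off, so redefinition of the primary composite is not called for.

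The separate component analyses (2.8.2) and the limitation about combining infection types (section 3) help a little, but neither isolates sepsis of unlisted source.

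**Conclusion.** The structure is as described: infections outside the four site definitions count only when organ dysfunction accompanies them, and the protocol links organ dysfunction to the exposure. Differential counting is therefore possible and plausibly biases away from the null.

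Its size cannot be derived from the document. On the main assumed inputs, a null odds ratio becomes about 1.03 to 1.2. It is exactly 1.00 if SOFA involvement is equal between groups, and reaches about 1.27 under the stronger non-extreme assumptions of the second set. Set beside 2.75, or an excess of at most 3.4 events in the main set beside a planned 21.5, this is probably modest. A reader might infer that the mechanism could by itself produce the hypothesised association; none of the scenarios, including the extreme one, comes close.

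The sample size is not in dispute. The labelling point in 2.5.3 holds whatever the size of the bias.

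**What to change.** Keep the primary composite and make three changes.

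1. Have the blinded panel record the source of every sepsis event, as one of the listed sites or other. The panel must already consider the source to judge that infection caused the SOFA change. Collect the field prospectively.
2. Prespecify in 2.9 a sensitivity analysis that repeats the primary model without counting events that qualify only through sepsis of unlisted source, and report how many such events occur in each exposure group. If the odds ratio barely moves, the result does not depend on severity-dependent counting.
3. Title 2.5.3 *deep incisional surgical site infection*, and word the conclusions to match what is counted.

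The cost is one extra CRF field, one extra model run and small wording changes. The sensitivity analysis will have slightly fewer events and so slightly less precision. Neither patient care nor the primary analysis changes.
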